### Randomization

2.5

This study will employ simple randomization to group participants. A third-party statistician will utilize SPSS version 22.0 to generate the randomization sequence, ensuring that researchers remain blinded to it. The random numbers are securely sealed in sequentially numbered opaque envelopes and stored in a double-locked cabinet. Upon completion of the baseline assessment and receipt of written informed consent, the envelopes will be opened sequentially in the order of enrollment to reveal group allocation. The allocation sequence will be maintained in strict confidentiality to prevent prediction of subsequent participants’ assignments.

### Blinding

2.6

Due to the obvious differences in moxibustion devices and procedures, blinding of participants and practitioners is infeasible. To mitigate bias associated with awareness of treatment allocation, outcome evaluators and data statisticians will remain blinded throughout the trial. In addition to patient-reported outcomes, infrared thermal imaging will be utilized as an objective secondary outcome measure to minimize subjective assessment bias. Unblinding will be permitted solely in the event of severe adverse events or upon the completion of data analysis.

### Interventions

2.7

A comparison of the intervention protocols between the moxa box moxibustion group and the Jianqiao ancient moxibustion group is illustrated in Figure 2.

**Figure 2 fig2:**
[figure not shown]
Comparison of intervention protocols between the control group and the experimental group.

#### Experimental group: Jianqiao ancient moxibustion treatment

2.7.1

Materials and equipment: Jianqiao ancient moxibustion specially formulated large moxa sticks (23 cm in length, 7 cm in diameter, and 500 g in weight), lighters, 75% alcohol cotton balls, and a specialized Jianqiao ancient moxibustion special moxibustion device. This device comprises a stainless steel three-hole box. Two horizontal rear holes are designed for moxa stick placement, and a vertical top hole connects to an exhaust fan and an external pipe to discharge smoke. The device is mounted on a height-adjustable stainless-steel bracket (Figure 3).Administering practitioner: Licensed acupuncturists with a minimum of 3 years of clinical experience will conduct Jianqiao ancient moxibustion. Prior to study initiation, all practitioners will undergo standardized training and successfully pass an assessment. To ensure intervention consistency, a unified protocol will be rigorously enforced.Preoperative precautions: The ambient temperature of the treatment room will be maintained at 26 °C. Moxibustion treatment will be postponed for patients who are fasting, have recently overeaten, or are experiencing acute exhaustion until they have sufficiently recovered.Operating procedures: ① Position selection: Patients will initially assume a sitting posture with their backs facing the device to expose the lumbodorsal treatment areas. After lumbar and dorsal moxibustion, patients will reposition themselves to face the device, exposing the abdominal treatment areas. ② Moxibustion area selection: The targeted areas include the Guanyuan area (bilateral 7-cm-diameter circular areas on the abdomen covering CV4), the spleen–stomach area (bilateral 7-cm-diameter circular areas on the back covering ipsilateral BL20 and BL21), the kidney area (bilateral 7-cm-diameter circular areas on the lumbodorsum covering ipsilateral BL23), and the baliao area (bilateral 7-cm-diameter circular areas at the lumbosacrum covering ipsilateral BL31, BL32, BL33, and BL34). The schematic diagram of the moxibustion areas is shown in Figure 4. ③ Disinfection: The treatment areas will be routinely exposed and disinfected three times with 75% alcohol cotton balls. ④ Moxa stick ignition: The specially formulated large moxa sticks will be ignited and inserted into the two horizontal holes of the device. The exhaust fan will be activated, and the device will be positioned 15 cm away from the patient’s body surface. ⑤ Moxibustion operation: Suspended moxibustion will be performed sequentially on the kidney area, spleen–stomach area, and baliao area. Each dorsal site will receive 15 min of moxibustion until the local skin becomes flushed. Patients will then turn to face the device and receive another 15 min of moxibustion on the Guanyuan area until local skin flushing occurs. ⑥ Postoperative handling: The device will be removed after moxibustion is completed. Patients will be advised to keep warm and rest adequately.Treatment frequency: Each of the four targeted acupoint areas will undergo moxibustion for 15 min, culminating in a total session duration of 60 min. The treatment protocol consists of three sessions per week for 4 consecutive weeks, resulting in a total of 12 sessions.

**Figure 3 fig3:**
[figure not shown]
Special moxibustion device for Jianqiao ancient moxibustion.

**Figure 4 fig4:**
[figure not shown]
Schematic diagram of the Jianqiao ancient moxibustion areas.

#### Control group: moxa box moxibustion treatment

2.7.2

Materials and equipment: Standard pure moxa sticks (10 cm in length, 1.5 cm in diameter, and 20 g in weight), lighters, 75% alcohol cotton balls, and wooden dual-hole moxa boxes.Administering practitioner: Licensed acupuncturists with a minimum of three years of clinical experience will administer the moxa box moxibustion. Prior to study initiation, all practitioners will undergo standardized training and successfully pass a competency assessment. To ensure intervention consistency, a unified protocol will be rigorously enforced.Preoperative precautions: The ambient temperature will be maintained at 26 °C. Moxibustion should be postponed for patients who are fasting, have overeaten, or are experiencing severe fatigue until they have sufficiently recovered physically.Operating procedures: ① Position selection: Patients will adopt a prone posture to expose the lumbodorsal treatment areas. After back moxibustion, they will switch to a supine position to expose the abdominal treatment areas. ② Moxibustion area selection: The Guanyuan area (bilateral 1.5-cm-diameter circular areas on the abdomen covering CV4), the spleen–stomach area (bilateral 1.5-cm-diameter circular areas on the back covering ipsilateral BL20 and BL21), the kidney area (bilateral 1.5-cm-diameter circular areas on the lumbodorsum covering ipsilateral BL23), the baliao area (two 1.5-cm-diameter circular areas per side at the lumbosacrum covering ipsilateral BL31, BL32, BL33 and BL34). ③ Disinfection: The treatment areas will be exposed and disinfected three times with 75% alcohol cotton balls. ④ Moxa stick ignition: Two moxa sticks will be ignited and inserted into the box holes, after which the box will be placed right above the targeted acupoints. ⑤ Moxibustion operation: Moxibustion will be applied sequentially to the kidney area, the spleen–stomach area, and the baliao area in a prone posture. Each area will be treated for 15 min until the local skin reddens and a mild warm sensation is felt. Patients will then turn supine and receive another 15-min moxibustion on the Guanyuan area following the same standard. Participants’ reactions will be closely monitored, and gauze will be placed under the box to relieve excessive heat stimulation if needed. ⑥ Postoperative handling: Following the session, the moxa box will be removed upon completion of treatment. Remaining moxa sticks and ashes will be properly disposed of, and patients will be advised to keep warm and rest adequately.Treatment frequency: Each of the four targeted acupoint areas will undergo moxibustion for 15 min, culminating in a total session duration of 60 min. The treatment protocol consists of three sessions per week for 4 consecutive weeks, resulting in a total of 12 sessions.

### Outcome measures

2.8

The assessment of outcomes encompasses the following domains: fatigue severity, TCM syndrome manifestations, symptoms of depression and anxiety, and body surface thermal characteristics. Assessments will be performed at baseline, immediately post-intervention (week 4), and during follow-up (week 16). Notably, infrared thermal imaging will be employed as an objective quantitative indicator, independent of subjective psychological perception, to evaluate body surface temperature distribution and thermal radiation characteristics along the meridians in each group.

#### Primary outcome

2.8.1

The primary outcome measure will be the Fatigue Scale-14 (FS-14). The FS-14 is a validated 14-item questionnaire for evaluating physical and mental fatigue. Each item utilizes a dichotomous yes-or-no response format and is scored as 0 or 1, with a total score ranging from 0 to 14. Higher scores will indicate more severe chronic fatigue (21, 22). FS-14 assessments will be performed at baseline, week 4 (post-intervention), and week 16 (follow-up).

#### Secondary outcomes

2.8.2

##### The Spleen–Kidney Yang Deficiency Symptom Scale

2.8.2.1

The Spleen–Kidney Yang Deficiency Symptom Scale is a 4-grade TCM syndrome rating scale. It evaluates both primary and secondary symptoms. Primary symptoms include aversion to cold and cold extremities, lassitude and lack of strength, shortness of breath and reluctance to speak, reduced food intake, and soreness and weakness of the lower back and knees; each item is scored from 0 to 6. Secondary symptoms include lumbar cold pain, abdominal fullness and distention, loose stools, cold, increased urine volume at night, teeth-marked tongue, and a deep, weak pulse, each scored 0–3. Higher total scores denote more severe Spleen–Kidney Yang Deficiency (23, 24). The Spleen–Kidney Yang Deficiency Symptom Scale will be administered at baseline, week 4 (post-intervention), and week 16 (follow-up).

##### Self-rating depression scale (SDS)

2.8.2.2

The SDS is a 20-item scale for assessing depressive symptoms, with total scores ranging from 20 to 80. Higher scores indicate greater depressive severity (25). The SDS will be administered at baseline, week 4 (post-intervention), and week 16 (follow-up).

##### Self-rating anxiety scale (SAS)

2.8.2.3

The SAS is a 20-item scale used to assess anxiety symptoms, with total scores ranging from 20 to 80. Higher scores indicate greater anxiety severity (26). The SAS will be administered at baseline, week 4 (post-intervention), and week 16 (follow-up).

##### Infrared thermal imaging detection

2.8.2.4

The distribution of body surface temperature is intricately linked to the functioning of visceral organs and meridians. Infrared thermal imaging, a non-invasive functional imaging modality, captures infrared radiation emitted by body surface tissues to depict superficial thermal characteristics (27). Infrared thermal imaging detection will be performed at baseline, week 4 (post-intervention), and week 16 (follow-up).

Instrument: The TTM-9000 medical infrared thermal imager (Hangzhou Xinhan Optoelectronics, Hangzhou, China) will be used. Its working waveband is 8–14 μm, the instantaneous field of view is ≤1.39 mrad, the temperature resolution is ≤0.1 °C, the measurement accuracy is ≤0.4 °C, and the detectable temperature range is 30–42 °C.Pre-scan preparation: ① The ambient temperature will be set at 26 °C with a relative humidity of ≤ 70%. The scanning room will be kept free of obvious airflow and strong infrared radiation sources. ② Participants will be instructed to refrain from strenuous exercise, irritant foods, and medications for 24 h before scanning and to refrain from eating and bathing within 1 h prior. Female participants will avoid menstruation. ③ Participants will be asked to empty their bowels and bladder and remove all clothing, glasses, and accessories. Females will have their hair tied up to expose their necks. The skin will be allowed to dry naturally for 10 min before image collection.Scanning protocol: ① Participant information will be registered in the supporting software. ② Participants will stand at the designated site for standard anterior and posterior trunk imaging. ③ The operator will adjust the camera parameters to acquire clear standard infrared thermal images. ④ Qualified images will be selected. The rectangular tool will be applied to delineate the Sanjiao and Governor Vessel regions. The division and zang-fu organs of the Sanjiao are presented in Table 3 (28). The mean temperature of each region will be recorded in an Excel spreadsheet. ⑤ All imaging data will be saved after confirmation.Data processing: Alterations in surface thermal distribution and the Governor Vessel radiation trajectory will be compared before and after the intervention. The mean thermal values and their differences will be calculated. Quantitative analysis will be performed using the corresponding software platform for subsequent statistical analysis.

**Table 3 tab3:** Division and zang-fu organs of Sanjiao.

Sanjiao subdivision	Anatomical scope	Zang-fu organs
Upper jiao	Above the diaphragm	Heart and lung
Middle jiao	From the diaphragm to the umbilicus level	Spleen, stomach, liver, and gallbladder
Lower jiao	Below the umbilicus	Kidney, large intestine, small intestine, and bladder

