**Discussion:**

It is hypothesized that Jianqiao ancient moxibustion will be more effective than moxa box moxibustion in alleviating symptoms in patients with CFS who have spleen–kidney yang deficiency. Furthermore, this study will employ infrared thermal imaging to assess alterations in the thermal characteristics of the Sanjiao and Governor Vessel both prior to and following moxibustion. This methodology may help elucidate the mechanisms underlying moxibustion’s modulation of yang-qi distribution in patients with CFS.

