### Trial design

2.1

This study is a single-center, single-blind, randomized controlled superiority trial. A total of 90 eligible participants diagnosed with CFS with a spleen–kidney yang deficiency pattern will be enrolled. Participants will be randomly assigned in a 1:1 ratio to receive either Jianqiao ancient moxibustion or moxa box moxibustion. The study will span 16 weeks, comprising a 4-week treatment period and a subsequent 12-week follow-up phase.

The trial is registered with the Chinese Clinical Trial Registry (ChiCTR2300079165). The trial flowchart is illustrated in Figure 1, and a detailed timeline is provided in Table 2.

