### Research hypothesis

2.3

Primary hypothesis: Participants receiving Jianqiao ancient moxibustion will demonstrate significantly greater improvement in fatigue severity than those in the moxa box moxibustion group.

Secondary hypothesis: Participants in the Jianqiao ancient moxibustion group will exhibit significantly greater improvements in TCM syndrome scores and reductions in anxiety and depression levels. In addition, favorable alterations in the infrared thermal characteristics of the Sanjiao and Governor Vessel are expected.

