Furthermore, this study aims to analyze the variations in the infrared thermal imaging characteristics of the Sanjiao and Governor Vessel before and after treatment. The Sanjiao plays a crucial role in the production, transformation, and distribution of qi, blood, body fluids, and essence, facilitating their upward, downward, outward, and inward movement. Through the transformation of qi by the Sanjiao, the zang-fu organs are interconnected, thereby regulating bodily functions and supporting all vital activities of the human body (41). In healthy individuals, the Sanjiao maintains a stable temperature rhythm, typically exhibiting an orderly gradient with a cooler upper jiao, a moderate middle jiao, and a warmer lower jiao, thereby preserving the physiological equilibrium of a cool upper and warm lower jiao (42). The Governor Vessel, often referred to as the “sea of all yang meridians,” plays a crucial role in regulating yang-qi throughout the body. It traverses the posterior midline and establishes a connection with the kidneys, thereby accumulating yang-qi to nourish internal organs and serving as a primary conduit for the transport of essence (43). Consequently, the surface infrared temperature and continuous thermal profile of the Governor Vessel can serve as indicators of whether systemic yang-qi is both sufficient and unobstructed (19, 44). Patients suffering from CFS typically exhibit distinct features in infrared thermal imaging, such as significant thermal deviations in the upper jiao, cooler deviations in the middle jiao, and a lack of continuity in the thermal line of the Governor Vessel (45). Therefore, detecting the infrared thermal characteristics of the Sanjiao and Governor Vessel can provide an objective assessment of the regulatory effects of moxibustion on yang-qi distribution and meridian thermal balance, while also offering insights into its underlying mechanism in the treatment of CFS.

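### The infrared before-after comparison is read as showing what moxibustion itself does, but both arms receive moxibustion, so the design supports only Jianqiao versus moxa box

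*Protocol article*

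**What the plan says.** Under data processing in section 2.8.2.4 (Infrared thermal imaging detection), the protocol article states: "Alterations in surface thermal distribution and the Governor Vessel radiation trajectory will be compared before and after the intervention". Mean regional temperatures and their differences are then passed on for statistical analysis.

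Other sections state what the images are for:

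- The abstract's Discussion says that infrared imaging will be used to "assess alterations in the thermal characteristics of the Sanjiao and Governor Vessel both prior to and following moxibustion", and adds: "This methodology may help elucidate the mechanisms underlying moxibustion’s modulation of yang-qi distribution in patients with CFS".
- The main Discussion (section 3) says that "this study aims to analyze the variations in the infrared thermal imaging characteristics of the Sanjiao and Governor Vessel before and after treatment", and concludes that these measurements "can provide an objective assessment of the regulatory effects of moxibustion on yang-qi distribution and meridian thermal balance", with insight into mechanism.
- The infrared sentence in section 2.3 (Research hypothesis) says that "favorable alterations in the infrared thermal characteristics of the Sanjiao and Governor Vessel are expected". It names no comparator, although the sentence before it is a between-group hypothesis.

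The design is in section 2.1: "Participants will be randomly assigned in a 1:1 ratio to receive either Jianqiao ancient moxibustion or moxa box moxibustion". Sections 2.7.1 and 2.7.2 give both arms four areas of the same names, 60-minute sessions and 12 sessions in total. Section 2.12 analyses data from multiple time points with a mixed model containing group, time and their interaction. It applies a Bonferroni correction across secondary outcomes.

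**The concern.** Randomisation protects one thing here: the difference between the two moxibustion types. A statement about what moxibustion as such does to surface temperature needs a comparison with no moxibustion, and the trial has none. What is left for that statement is change over time within patients who were all treated. That change mixes any treatment effect with the natural course of a fluctuating condition and with whatever else differs between the scans.

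The conclusion is what is at stake. Participants and practitioners are unblinded and the primary outcome is a questionnaire, so sections 2.6 and 2.8 present infrared imaging as the objective measure. An objective instrument removes reporting bias, but it does not turn an uncontrolled before-after change into a treatment effect. A report that follows the present wording could offer within-patient thermal change as objective evidence that moxibustion regulates yang-qi distribution, which the design cannot establish. The limitations in section 3 cover blinding, single centre with small sample, and restriction to one TCM pattern. They do not mention the missing non-moxibustion control.

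**Working it through.** **Step 1: what each contrast estimates.** Let D be the mean change from baseline that would occur without any moxibustion (natural course, fluctuation, other time effects). Let m_J and m_B be the effects of Jianqiao and moxa box relative to no moxibustion.

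- Within-arm change, Jianqiao: D + m_J
- Within-arm change, moxa box: D + m_B
- Average change over both arms (time effect): D + (m_J + m_B)/2
- Between-arm difference in change (group by time): (D + m_J) − (D + m_B) = m_J − m_B

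There are two observable arm means and three unknowns, so only m_J − m_B is identified. D drops out of the between-arm difference, but so does any effect that the two types share. Fitting the model in section 2.12 does not alter this, because its time effect still contains D.

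**Step 2: the plan's own figures.** The protocol gives no calculation for the infrared outcome. Its only computed figure is the FS-14 sample size in section 2.11, used here for the number of completers:

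- pooled SD = √((1.43² + 2.73²)/2) = 2.18
- d = (6.23 − 4.86)/2.18 = 0.63
- 40 per group by the normal approximation
- 40/0.90 = 44.4, rounded up to 45 per group, 90 in total

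This reproduces the stated figures. The point does not depend on them.

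**Step 3: illustration of how a within-arm test would behave with m_J = m_B = 0.** Inputs:

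- n = 40 completers in one arm (section 2.11).
- Drift D of 0.2, 0.3 or 0.4 °C: assumed. For scale, section 2.8.2.4 gives the imager's accuracy as ≤0.4 °C.
- SD of change of 0.7 or 1.0 °C: assumed.
- Two-sided level 0.05, or 0.05/4 = 0.0125 if Bonferroni is taken over the four named secondary outcomes (assumed, because section 2.12 does not give the divisor).

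Formula: paired t-test, noncentrality = D/(SD/√40), power from the noncentral t distribution with 39 degrees of freedom. Example: 0.2/(0.7/√40) = 1.81 against a critical value of 2.02, giving 42%.

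| Level | SD (°C) | D = 0.2 | D = 0.3 | D = 0.4 |
|---|---|---|---|---|
| 0.05 | 0.7 | 42% | 75% | 94% |
| 0.05 | 1.0 | 23% | 46% | 69% |
| 0.0125 | 0.7 | 22% | 54% | 83% |
| 0.0125 | 1.0 | 10% | 25% | 47% |

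Under the same assumptions the between-arm test stays at its nominal level, because a shared drift cancels.

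**The case against.** The strongest reply is that the valid analysis is already in the plan. The before-after sentence stands under data processing, and the analysis itself is the mixed model of section 2.12, whose interaction term is the randomised contrast. No standalone paired infrared test is specified. The abstract says only that the method may help, the strongest claim is in a Discussion paragraph, and the trial's overall aim is comparative.

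Much of this stands. A reader might infer that the infrared analysis consists of within-arm tests, or that the infrared data are uninterpretable. The documents support neither. What the reply does not remove is that the Methods describe the infrared comparison as before versus after, that section 2.12 also evaluates temporal differences, and that both discussions attach the result to moxibustion rather than to one type against the other.

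Three further inferences are tempting and should not be drawn:

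- **That both arms will probably warm and so produce a false positive.** Nothing in the documents says so. Section 3 describes the healthy state as a gradient across regions, so uniform warming would not plainly count as favourable.
- **That regression to the mean is established.** No one is selected on skin temperature, and section 2.4.1 makes no single cold symptom mandatory.
- **That season must be modelled.** Section 2.8.2.4 fixes the scan room at 26 °C and humidity at 70% or below, and controls airflow and preparation. Entry over a study period from January 2024 to November 2026 could make seasonal shifts partly cancel. A shift shared by the arms drops out of the between-arm contrast anyway, so a season covariate is not needed.

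**Conclusion.** The point holds in a limited form. The infrared wording in sections 2.8.2.4 and 3 and in the abstract promises information about moxibustion's own effect and mechanism. A trial with two moxibustion arms cannot identify that effect, whatever analysis is applied. It can show whether Jianqiao alters the thermal measures more than moxa box does. Equally, finding no between-arm difference would not show that moxibustion has no thermal effect.

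This conclusion rests on the allocation alone and needs no numerical assumption. The percentages (23% to 94% at 0.05, 10% to 83% at 0.0125) depend wholly on the assumed drift and SD. They show that a within-arm p-value can be uninformative about treatment, not that it will mislead in this trial. The matter concerns one secondary, mechanistic outcome. It is worth correcting because it changes what the trial may conclude at almost no cost.

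**What to change.** 1. In section 2.8.2.4, and in the infrared sentence of section 2.3, name the between-arm difference in change from baseline, taken from the section 2.12 model, as the only inferential infrared comparison.
2. Report within-arm changes and the model's time effect descriptively, without significance tests.
3. In the abstract's Discussion and in section 3, limit the infrared conclusion to Jianqiao versus moxa box, with no claim about the effect or mechanism of moxibustion as such.
4. Add the absence of a non-moxibustion control to the limitations in section 3.

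This is a change of wording. It needs no new data, visits or participants. The price is a narrower mechanistic claim.
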